8.2 Secondary Outcome

Descriptive analysis of the campaign questionnaire results will be conducted. Chi-square test will be used to analyze differences between comparison groups for categorical variables and t-test will be used for nominal variables.

Missing outcome data will be assumed to be "missing at random", conditional on key predictors of "missingness" (in particular, Baseline values, Intervention Group, and measures of compliance post-randomisation). Multiple imputations of outcome variables will be carried out using these predictors of "missingness".

1. **Feasibility Study Management**
   1. Day-to-day Management

The Coordinating Centres are located across the two sites, Élisabeth Bruyère Research Institute and the Ottawa Health Research Institute, in Ottawa. Personnel will include the co-principal investigators, project manager, research assistants, statistician, data analysts, and data entry staff. The Coordinating Centres are responsible for the day-to-day management of the trial.

The Guide Facilitator will be the project manager or their delegate, with an effort made to have a provincial facilitator available to coordinate the study in each participating province. The provincial facilitators liaise with each organization, collecting all data and ensuring the organization has access to facilitators as needed.

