1.4 Research Question

Among healthcare organizations who conduct Seasonal Influenza Immunization Campaigns, does use of the Guide impact the effectiveness of these campaigns as measured by change of healthcare personnel immunization rates and in an organization’s ability to plan, implement, monitor, and evaluate their campaign?

- 1. Research Objectives

1. To assess any changes in healthcare personnel immunization rates between the Control Group (usual campaign) and the Intervention Group (campaigns using the Guide)
2. To assess if, by tracking immunization rates by direct patient category, healthcare organizations are better able identify lower or higher immunization rates among the healthcare personnel who have the most direct patient contact (16)
3. To assess the effectiveness of the Guide. We will do this by assessing the Intervention Groups’ ability to make the changes in campaign planning, implementation, monitoring, and evaluation using the recommendations in the Guide
4. We will assess the delivery methods of the Guide (paper, web-based) and assess the Intervention Group’s satisfaction with ease of use, practicality of application, and need for outsider intervention
5. **Methods**
   1. Trial Design

This will be a multi-centre, cluster, randomized controlled trial.

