This Intervention Group will be invited to participate in either a half-day workshop or Webinar in September 2010 and September 2011. Ideally, this will be done in partnership with the Canadian Coalition on Immunization Awareness and Protection (CCIAP), public health and regional health authorities. The purpose of this intervention is to provide a basic introduction to the Guide and introduce the Guide Facilitator. The Intervention Group will be given access to the website and access to the Guide.

In March 2011 and again in March 2012, they will be asked to report their influenza immunization rates and complete an evaluation of the Guide.

In October, January and March of each campaign year, there will be a Webinar or Teleconference with the Intervention Group to answer questions, share challenges, and establish a community of practice. The Group, or subsets of the Intervention Group, may choose to meet more often and will be invited to participate in a web-based chat forum moderated by the Guide facilitator or their delegate.

- 1. Control Group

For the control group, the team will register the organization and will collect their immunization rates, baseline organizational data, and campaign activities for 2008-2009. We will contact them in March 2011 and March 2012 to collect immunization rate data and report on campaign activities. We will ask them open-ended questions to determine the content and process used in their more recent campaigns based on the focus group results from our work with the 16 organizations in 2009-2010.

They will be given access to the public part of the CHIIN website, and will be encouraged to calculate their immunization rates using the methodology in Appendix 3 of the Guide (16). This information will be publically available by September 2010.

The Control Group will be given access to the Guide at the end of the two-year period. In terms of contamination, Control Group participants may be disappointed and seek their own way of increasing immunization rates among healthcare personnel. The final unstructured interviews should capture this information.

- 1. Questionnaires

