**Control Group – September 2010**

- Registration Form
- Immunization rate data for 2008-2009

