**Control Group – March 2011 and March 2012**

- Immunization rate data for each year
- Answer open-ended question re: campaign activities

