**Intervention Group – September 2010**

The following questionnaires will be given before campaign begins:

- Registration Form
- Campaign Details Questionnaire
- Immunization rate data for 2008-2009

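### Section 8.2 plans between-group tests next to the campaign questionnaire, but only the Intervention Group gets the structured campaign form, and the t-test is assigned to nominal variables

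*Protocol*

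**What the plan says.** The research question (protocol, section 1.4) has two parts: whether the Guide changes immunization rates, and whether it changes an organization's "ability to plan, implement, monitor, and evaluate their campaign".

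Section 8.2 opens with "Descriptive analysis of the campaign questionnaire results will be conducted" and continues directly with "Chi-square test will be used to analyze differences between comparison groups for categorical variables and t-test will be used for nominal variables".

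The Questionnaires section lists the instruments by arm and date. The Intervention Group receives the "Campaign Details Questionnaire" before the first campaign, and the same form appears in its lists for March 2011 and March 2012. The Control Group's September 2010 list has a registration form and "Immunization rate data for 2008-2009". Its list for the two March rounds has yearly rates and "Answer open-ended question re: campaign activities".

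The Control Group subsection under Interventions says that the team "will collect their immunization rates, baseline organizational data, and campaign activities for 2008-2009". It adds that controls will report their activities in March 2011 and March 2012 in reply to open-ended questions.

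**The concern.** A between-group test needs the same variable measured in both arms. As scheduled, one arm completes a structured form and the other writes free text. If 8.2 is meant for the campaign form, its comparison has no matching control data. An answer to the campaign-management part of the research question would then be either a comparison across different instruments or a before-after description in the Intervention Group. Randomization protects against neither problem.

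Two smaller defects sit alongside. The text and the September 2010 list do not agree on whether, or with what form, control campaign activities for 2008-2009 are collected. The t-test is also assigned to a type of variable on which it cannot be used.

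**Working it through.** The protocol gives no figure on this point to reproduce, so the check sets the schedule against the analysis.

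**1. Instruments for campaign activities, by arm and round** (Questionnaires section and Control Group subsection)

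| Round | Intervention Group | Control Group |
|---|---|---|
| September 2010 | Campaign Details Questionnaire | None listed by name; the text promises 2008-2009 activities |
| March 2011 | Campaign Details Questionnaire | Open-ended question |
| March 2012 | Campaign Details Questionnaire | Open-ended question |

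Scheduled rounds of the structured form: 3 in the Intervention Group, 0 in the Control Group.

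**2. What the test needs.** A chi-square test of one questionnaire item compares response counts by arm. For any item of the Campaign Details Questionnaire the control counts are empty. They could be filled only by coding control free text to the same items. The protocol does not plan that; it says open-ended answers will be summarized in a yearly post-campaign report.

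**3. Direction of bias if free text is coded.** In a post-campaign comparison, unprompted answers may leave out activities that a check-box would elicit, which would lower the control counts. The tertiary outcome, however, is improvement over time. The Intervention Group is prompted at baseline as well as at follow-up, so prompting may partly cancel in its change score. The control baseline instrument is not known. The net direction for change therefore cannot be derived from the protocol.

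**4. Control baseline.** The Control Group subsection promises "baseline organizational data, and campaign activities for 2008-2009"; the September 2010 control list names only the registration form and past rates. The two agree only if the registration form carries the campaign items, and its content is not shown.

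**5. The t-test.** A t-test compares means. Nominal categories have no mean, and as categorical variables they already fall to the chi-square test in the same sentence. Section 8.1 uses the t-test properly, on mean differences in rates, so the word is probably a slip for continuous.

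**6. What a like-for-like comparison could show.** The Sample Size section gives 46 organizations with 23 in the Intervention Group, leaving 46 − 23 = 23 controls. For one yes/no item, power is about Φ[(|p2 − p1| − 1.96·SE0)/SE1], where SE0 = √(2p̄(1 − p̄)/23) and SE1 = √([p1(1 − p1) + p2(1 − p2)]/23). The rates below are assumptions; the protocol gives none for campaign activities.

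| Control | Intervention | SE0 | SE1 | Power |
|---|---|---|---|---|
| 50% | 70% | 0.144 | 0.141 | 28% |
| 50% | 80% | 0.141 | 0.134 | 57% |
| 50% | 90% | 0.135 | 0.122 | 87% |

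Even with the same form in both arms, only large differences on a single item would be detected reliably.

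**The case against.** The strongest reply is that 8.2 does not say the chi-square test applies to the Campaign Details Questionnaire. The section is headed Secondary Outcome, and Study Outcomes defines that outcome as better reporting of immunization rates, with data from both arms. The Questionnaires section says check-box items will be analysed descriptively. Objective 3 looks only at the Intervention Group, and campaign management is a tertiary outcome. On that reading the test can be computed.

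This stands in part: the link to the questionnaire is the natural reading of two adjacent sentences, not an explicit statement. If another reading was intended, however, 8.2 needs to say so, and the campaign-management part of the research question would still have no like-for-like comparison between arms.

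Open-ended questioning of controls may also be deliberate. The protocol builds it on focus groups with 16 organizations and discusses contamination. A structured form in September 2010 or March 2011 could prompt controls before a study campaign. That stands, and it limits when the form can safely be given.

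A reader might infer three stronger things that the protocol does not support:

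- That there are no control data on campaigns. Controls report activities in free text in both March rounds, final unstructured interviews are mentioned, and 2008-2009 activities are promised.
- That none of the 23 control organizations supplies any structured campaign item. The registration form is not shown and may contain some.
- That the mismatch favours the Guide. Step 3 of the working shows why this is open for change from baseline.

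Nor can the matter be left to a statistical analysis plan. The protocol fixes which arm receives which form, and an analysis plan cannot recover answers that were never collected.

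**Conclusion.** The point holds in a limited form. The structured campaign form is scheduled in three rounds for one arm and in none for the other. On its natural reading, the between-group comparison in 8.2 has no comparable structured control data. The campaign-management part of the research question would rest on unlike instruments or on the Intervention Group alone. The size and direction of any bias are not established.

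This rests on two assumptions: that the sentence with the chi-square test refers to the questionnaire named just before it, and that the registration form does not duplicate the campaign form. The second matters for baseline only, since no registration form is listed in March. The primary analysis of immunization rates is not touched.

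The t-test wording is wrong on any reading, but it is a one-word correction and adds no weight to the design point.

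**What to change.** 1. Give the Campaign Details Questionnaire to both arms at least in March 2012, and collect it from controls before they receive the Guide. The last study campaign is over by then, so the form cannot influence a later one. Section 8.2 then has a randomized post-campaign comparison on one instrument.
2. If that is not wanted, limit 8.2 to description within the Intervention Group and narrow the research question in 1.4 to match.
3. Reconcile the Control Group subsection with the September 2010 control list: either name the instrument that collects 2008-2009 campaign activities or withdraw the promise.
4. In 8.2, state which variables the between-group tests cover, and assign the t-test to continuous variables.

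The cost of the first change is one more self-administered form, already available online or by email, for about 23 organizations. Controls would still have no structured baseline or Year One data, so the comparison is of March 2012 status and not of change. The Intervention Group would also be completing the form for the third time and controls for the first. Adding earlier control rounds would supply change data, at the price of possibly prompting controls before a study campaign. The other changes are edits to the text.

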# Data Management

Data collected from the web-based questionnaires will only be accessible to the project team using a secured password. Discussion notes from the workshops, webinars or teleconferences will not include any personal identifiers and will be kept by the project manager for the duration for the study.

1. **Ethical Issues**

- 1. Research Ethics Board Approvals

Ethics approval of this study will be obtained within the context of the CIHR by the Coordinating Centre sites by The Ottawa Hospital Research Ethics Board and the Bruyère Continuing Care Research Ethics Board. Ethics approval will be obtained from each participating organization only if required by them.

The Research Ethics Boards will be notified of any changes are made to the study protocol, and no activity will take place before ethical approvals are obtained.

- 1. Informed consent

No individual informed consent will be required. This study is a feasibility study of new tools for use by healthcare organizations within their established influenza immunization campaigns. No personal individual information will be collected.

- 1. Confidentiality

1. Some sites in the Intervention Group may choose to collect the OIDA and send to the Coordinating Centre for reference. No personal information is collected on the OIDA and its completion is completely anonymous.
2. All study data will be anonymized. Electronic data will only be accessible by appropriate study personnel and password protected. Digital transcripts will be sent for transcription with an authorized transcriptionist, with all identifying material removed. All paper data is held behind locked doors in locked cabinets and accessible to study personnel only.
3. Any workshop, webinar and teleconference transcripts may be recorded digitally and meeting notes will be taken. After all identifying information has been removed, the transcripts may be used for qualitative analysis, including coding for themes using nVivo software. The digital records will be kept for three years. The paper records will be kept with the rest of the study documentation for 15 years after termination of the study.
4. The names of the organizations that may audit study records include the Ottawa Hospital Research Institute, the Élisabeth Bruyère Research Institute, the Bruyère Continuing Care Research Ethics Board, The Ottawa Hospital Research Ethics Board, and the Canadian Institutes of Health Research.
5. The study records will be kept for 15 years after termination of the study. Paper documents will be shredded and electronic files deleted.

#

1. **Publication of Results**

The results of this study will be published in peer-reviewed healthcare journals and will be presented at scientific conferences.

